## **Abstract**

### **Background**

Knee osteoarthritis (OA) is a prevalent disabling disorder that involves changes in articular cartilage damage, subchondral bone remodeling, synovitis, and abnormal infrapatellar fat pad (IPFP). Due to the complicated etiology and numerous phenotypes of knee OA, limited improvement is achieved for treatments among knee OA patients with different phenotypes. Inflammatory OA phenotype is a typical knee OA phenotype, and individualized treatment targeting on inflammation is a promising way to obtain an optimal therapeutic effect for people with inflammatory knee OA phenotype. Glucocorticoid is a traditional anti-inflammatory drug for knee OA and intra-articular glucocorticoid injections are recommended clinically. However, emerging evidence has shown the repeated intra-articular glucocorticoid injections for a long term would induce cartilage loss. IPFP and its adjacent synovium are considered as the main source of inflammation in knee OA. This GLITTERS trial aims to investigate if a glucocorticoid injection into the IPFP is effective and safe over 12 weeks among knee OA patients with an inflammatory phenotype.

### **Methods**

GLITTERS is a multicenter, double-blinded, randomized, and placebo-controlled clinical trial among knee OA patients with both Hoffa-synovitis and effusion-synovitis. Sixty participants will be allocated randomly and equally to either the glucocorticoid group or the control group. Each group will receive an injection of glucocorticoid or saline into the IPFP with an intra-articular hyaluronic acid injection as a background treatment at baseline, and be followed 4, 8, and 12 weeks. Primary outcomes will be changes in knee pain on a visual analogue scale and effusion-synovitis volume measured on magnetic resonance imaging (MRI). Secondary outcomes will be changes in the total score of Western Ontario and McMaster Universities Osteoarthritis Index score, MRI-detected Hoffa-synovitis score, quality of life, pain medication use, IPFP

volume, and the incidence of adverse reactions. Data analyses based on the intention-to-treat principle will include mixed-effects regressions, Wilcoxon rank-sum tests, and chi-square tests (or Fisher's exact test).

## **Introduction**

Osteoarthritis (OA) is a highly prevalent joint disease characterized by joint pain and structural changes which ultimately lead to loss of joint function. According to the estimation of the World Health Organization, there are about 300 million OA patients worldwide, and the prevalence of OA among people over 50 years old can reach up to 10-20%. Knee OA is the predominant type of OA whose pathological changes include articular cartilage damage, subchondral bone remodeling, synovitis, and abnormal infrapatellar fat pad (IPFP, or Hoffa's fat pad). Knee OA seriously decreases the quality of life of the patients and leads to a heavy economic burden to patients' families as well as society.

However, there is no curative drug for knee OA. Apart from some patients with end-stage knee OA undergoing total knee arthroplasty, most patients choose conservative treatments to alleviate their symptoms. Due to the complicated etiology and numerous subtypes of knee OA, limited improvement is achieved for similar treatments among patients with different knee OA phenotypes. Therefore, an individualized treatment focusing on a specific phenotype of knee OA is a promising way to obtain an optimal therapeutic effect.

Inflammatory phenotype is one of the most typical phenotypes of knee OA. IPFP and synovium as a structural complex are considered as the main source of inflammation in knee OA. IPFP, an adipose tissue, is below the patella and located closely to the synovial layers. Adipocytes and immune cells are abundant in IPFP. Abnormal IPFP can release a variety of inflammatory products which result in changes of cartilage, synovium, and subchondral bone, and eventually accelerate OA progression. Signal changes in IPFP detected by magnetic resonance imaging (MRI)

are referred to as Hoffa-synovitis. Effusion-synovitis, a composite of joint fluid and synovial thickening, refers to the MRI-detected signal changes in the synovial cavity. Abundant clinical evidence showed that Hoffa-synovitis and effusion-synovitis were associated with the incidence and progression of knee OA. Therefore, anti-inflammatory therapies for those knee OA patients with Hoffa- and effusion-synovitis may have a better clinical effect.

Glucocorticoid is a traditional anti-inflammatory drug for knee OA. It suppresses inflammation via the apoptosis induction of immune cells and the suppression of the proinflammatory mediators expression. Clinically, intra-articular glucocorticoid injections are recommended for people with knee OA to reduce their pain. However, emerging evidence has shown that repeated intra-articular injections over two years would induce more cartilage loss. Thus, the injection of glucocorticoid into IPFP may not only play a better role in anti-inflammatory but minimize the cartilage deterioration among inflammatory knee OA patients. To date, there is no study about the injection of drugs into IPFP.

The characteristics of real-time imaging and tracking in ultrasonography make the injection into inflammatory sites of IPFP possible. Therefore, we hypothesized that the IPFP injection of glucocorticoid can effectively reduce the knee pain and effusion-synovitis volume, compared to the placebo injection among people with symptomatic knee OA who have effusion- and Hoffa-synovitis.

## **Objectives**

The primary aim is to assess whether the injection of glucocorticoid into the IPFP can effectively reduce the knee pain measured by visual analogue scale (VAS) and MRI-measured effusion-synovitis volume, compared to the placebo injection among patients with symptomatic knee OA who have both effusion- and Hoffa-synovitis.

Secondary aims are to evaluate whether the injection of glucocorticoid into the IPFP effectively reduces the total Western Ontario and McMaster Universities Osteoarthritis Index (WOMAC) score, MRI-assessed Hoffa-synovitis score and pain

medication use, improves the quality of life, and has difference in IPFP volume and adverse reaction, compared to the placebo injection among symptomatic knee OA patients with both effusion- and Hoffa-synovitis.

## Methods and analysis

### Study design

GLITTERS is a multicenter, randomized, double-blind, placebo-controlled trial over 12 weeks (figure 1). The ethics approval in all four centers has been received from the Medical Ethics Committee before the recruitment. The principal study center is Zhujiang Hospital of Southern Medical University (2021-KY-183-02), and the other study centers are the Sixth Affiliated Hospital of Sun Yat-sen University (2022ZSLYEC-179), the Third Affiliated Hospital of Sun Yat-sen University ([2022]02-138-01), and Beihai People's Hospital (2022-014). This study will use competitive enrollment, and all participants will provide informed written consent prior to data collection. The trial will be reported in accordance with the Consolidated Standards of Reporting Trials guidelines.

[figure not shown]

**Figure. Flowchart of the trial.**

## **Recruitment and informed consent**

The potential participants will be recruited in the following ways: 1) referrals by the participating doctors from outpatient clinics; 2) public education from the surrounding community hospitals; 3) posters/flyers placed on hospitals and surrounding communities; and 4) electronic advertisements on social media platforms. Each participant will be asked to sign two copies of the informed consent to ensure that their participation is voluntary. One copy is preserved by the principal researcher, and the other by the participant.

## **Eligibility criteria**

Inclusion criteria:

- 1) Diagnosed with symptomatic knee OA according to American College of Rheumatology criteria;
- 2) Age > 45 years;
- 3) Have knee pain for more than six months and the pain assessed by VAS (100 mm)  $\geq 40$  mm in last week;
- 4) Ultrasonography showed obvious synovitis (over about 10 ml) with effusion in the knee joint;
- 5) Both MRI-assessed Hoffa-synovitis score (MRI Osteoarthritis Knee Score, MOAKS method) and effusion-synovitis score (MOAKS method)  $\geq 1$ , and their total score  $\geq 3$ ;
- 6) Being able to listen, speak, read and understand Chinese, capable of understanding the study requirements and cooperating with the researchers during the study, and providing written informed consent.

### Exclusion criteria

- 1) Allergy to glucocorticoids;
- 2) Knee joint injection of glucocorticoid or hyaluronic acid within the past six months;
- 3) Severe trauma or arthroscopy in the knee within the past six months;
- 4) Planned hip or knee surgery (including arthroscopy, arthroplasty, and other open joint surgeries) in the next six months;
- 5) Contraindication to having MRI (e.g., implanted pacemaker, artificial metal valve or cornea, aneurysm clipping surgery, arterial dissection, metal foreign bodies in the eyeball, claustrophobia);
- 6) Presence of other arthritis, such as rheumatoid arthritis and psoriatic arthritis;
- 7) Other condition that is more painful than their knee OA;
- 8) Malignant tumors or other life-threatening diseases;
- 9) Infection, diabetes, coagulopathy, osteonecrosis, or gastric/duodenal ulcer within the past 12 months;
- 10) Current use of oral corticosteroids, nonsteroidal anti-inflammatory drugs, or immunosuppressive medication;
- 11) Pregnancy or lactating female;
- 12) Use any investigational drugs or devices in the recent 30 days.

Note: When both knees of the participants meet the eligibility criteria, the knee with more severe VAS pain will be selected as the study knee.

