## **Intervention**

Participants are randomly allocated to either treatment (glucocorticoid) group or placebo (saline) group. Each group will receive two injections at baseline: one is the glucocorticoid or saline into IPFP, and the other is intra-articular hyaluronic acid as a background treatment.

The product of the glucocorticoid is betamethasone injectable suspension (Diprosone) and the dosage is 1 ml. To alleviate the discomfort on local tissues, the suspension injected into the IPFP will be pre-mixed with 0.5 ml saline and 0.5 ml lidocaine (concentration: 2%). That is, the total amount of the drug injected into the IPFP for the glucocorticoid group will be 2.0 ml. Accordingly, a total of 2.0 ml drug including 1.5 ml saline and 0.5 ml lidocaine will be injected into the IPFP in the placebo group. The injection of glucocorticoid or placebo into the IPFP will be performed under the guidance of ultrasonography. The procedures are as follows: 1) the participant lies on the bed with a small pillow behind his/her knee to bend the knee joint by 20-30°; 2) the ultrasonic probe is placed under the patella to show the IPFP and its inflammatory sites (figure 1); 3) insert the needle through the inferior lateral patella; 4) the drug is injected on two sites at the bottom of IPFP near the synovium where synovial hyperplasia is obvious, with a dosage of 1 ml at each site. All physical therapists will be trained for this injection under the supervision of an experienced therapist.

The intra-articular hyaluronic acid (ARTZ, Seikagaku Corporation, Japan) injection will be added as a background treatment. That is, after completing the process

of IPFP injection, the participants in both groups will receive 2.5 ml hyaluronic acid suspension injection through the suprapatellar bursa into the intra-articular space under the guidance of ultrasonography.

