\* The participants will complete the questionnaires (VAS, WOMAC, AQL-4D, an PHQ-9) of the follow-ups at home and send back to researchers. As for pain medication use, use of medication & supplements, and adverse events, the researchers will ask the participants via remote interview.

# In MRI.

† Including names, gender, birth date, height, weight and contact details.

§ Diagnosis of symptomatic knee osteoarthritis according to American College of Rheumatology criteria.

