## Questionnaires and queries

The VAS (100 mm visual analog scale) will be used to assess knee pain using the standard question: “On this line, how would you rate your knee pain in the last week?”. A higher score indicates a higher level of pain severity.

The WOMAC requires patients to rate their pain (five items), stiffness (two items), and functional dysfunction (17 items) in the last week. Each item is a 100-mm visual analog scale. The WOMAC score is calculated by summing the score of each

item with every 1 mm representing one point. A higher WOMAC score indicates a more severe OA symptom. When more than five items are not completed, the WOMAC score would be regarded as missing data. Otherwise, the WOMAC score would be calculated by averaging the remaining score and then multiplying by 24.

The AQL-4D will be used to assess the quality of life in the last week. It comprises four dimensions of independent living, social relationships, psychological well-being, and physical senses. Each dimension has three items with four response categories ranging from 0-3. The total AQL-4D score ranges from 0-36, and a higher score indicates a lower quality of life.

The PHQ-9 will be used to assess the depression in the last two weeks. It comprises nine items with four response categories scored from 0-3. The total PHQ-9 score ranges from 0-27, and a higher score indicates a more severe depression level.

Queries about medications and supplement use will also be recorded at baseline and each follow-up. Adverse events and reactions will be recorded at each follow-up. Pain medication use would be determined by the researchers from the records of medication use. Adverse events are defined as any untoward event occurring during the trial, regardless of its relation to treatment, and they need to be reported spontaneously when they occur. Details of the adverse event will be recorded and whether it is an adverse reaction will be determined.

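### The allergy exclusion names glucocorticoids only, although both arms are also injected with lidocaine and hyaluronic acid (minor, cheap to fix)

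*Combined protocol and SAP*

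**What the plan says.** Item 1 of the protocol's Exclusion criteria reads "Allergy to glucocorticoids". SAP section 5.1 (Eligibility) carries the same list with the same item.

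The Intervention section describes two injections at baseline for every participant:

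- **Fat-pad injection, glucocorticoid arm:** "the suspension injected into the IPFP will be pre-mixed with 0.5 ml saline and 0.5 ml lidocaine". The lidocaine is at 2%.
- **Fat-pad injection, placebo arm:** "a total of 2.0 ml drug including 1.5 ml saline and 0.5 ml lidocaine will be injected into the IPFP".
- **Joint injection, both arms:** "the participants in both groups will receive 2.5 ml hyaluronic acid suspension injection".

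Hyaluronic acid appears once in the exclusions, in item 2: "Knee joint injection of glucocorticoid or hyaluronic acid within the past six months". That is a washout rule for earlier injections and says nothing about allergy.

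**The concern.** The written rule screens for allergy to the product that 30 of the 60 participants are planned to receive. It omits the two products that all 60 are planned to receive. A screener who follows the list exactly would admit someone with a known allergy to lidocaine or to hyaluronic acid, whichever arm that person then joined.

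What is at stake is participant safety, on a small scale. There is also a minor knock-on for the data: Randomization and blinding permits emergency unblinding after a serious adverse event and withdraws the unblinded patient, so a severe reaction could cost a participant. Under Audits and steering, the trial has no Data Monitoring Committee because the intervention is considered low-risk, so the entry criteria are one of the main written safeguards.

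**Working it through.** There is no figure in the plan to reproduce on this point. The check is a comparison of the products injected with the criteria that could exclude an allergic person, followed by a rough size under a stated assumption.

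**Step 1. Products against allergy criteria.**

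| Product | Glucocorticoid arm | Placebo arm | Allergy exclusion |
|---|---|---|---|
| Betamethasone suspension | 1 ml | none | Item 1 |
| Lidocaine 2% | 0.5 ml | 0.5 ml | None |
| Hyaluronic acid | 2.5 ml | 2.5 ml | None |

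**Step 2. Could another criterion close the gap?** These are the nearest candidates, in the protocol and in SAP 5.1:

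- Exclusion 2 is the six-month washout.
- Exclusion 5 deals with contraindications, but only to MRI.
- Exclusion 8 covers malignancy and life-threatening disease, which is not an allergy rule.
- Inclusion 6 covers language, cooperation and consent.
- There is no catch-all or investigator-discretion item.

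None covers a known allergy to lidocaine or hyaluronic acid. Both eligibility lists are shown in full, so this is not an extraction gap.

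**Step 3. Could a stated baseline procedure close it?**

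- Table 1 schedules clinical evaluation and history collection at screening/baseline. Its footnote explains the clinical evaluation as "Diagnosis of symptomatic knee osteoarthritis according to American College of Rheumatology criteria". The footnote mark sits on the clinical evaluation, so it does not limit the history; the content of the history is simply not described.
- Questionnaires and queries adds "Queries about medications and supplement use will also be recorded at baseline and each follow-up", which concerns products taken, not reactions to them.

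An allergy question may be asked, but neither document states it.

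**Step 4. Size, under an assumption.** The documents give no prevalence, so take *p*, the share of candidates with a known allergy to either product, as 0.1% to 1%. Suppose that such people enrol like anyone else and that nobody catches the allergy. With *n* = 60, the expected number is *np* and the chance of at least one is 1 − (1 − *p*)^60.

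| Assumed *p* | Expected number | Chance of at least one |
|---|---|---|
| 0.1% | 60 × 0.001 = 0.06 | 1 − 0.999^60 = 5.8% |
| 0.5% | 60 × 0.005 = 0.30 | 1 − 0.995^60 = 26.0% |
| 1% | 60 × 0.01 = 0.60 | 1 − 0.99^60 = 45.3% |

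These figures follow directly from the assumed *p* and are upper bounds for it. They are not evidence that the gap is filled by real patients.

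**Step 5. Effect on the statistics.** The sample size rests on a difference of 19.9 mm, a standard deviation of 24.2 mm, two-sided alpha of 0.05, 80% power and 20% loss: 2 × [(1.96 + 0.842) × 24.2 / 19.9]² = 23.2, rounded up to 24 per arm, and 24 / 0.8 = 30. None of these inputs depends on the allergy criterion. Both omitted products go to both randomised arms, so the comparison is not biased.

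**The case against.** The strongest case on the other side is that this is drafting preference. The glucocorticoid is the product under test, lidocaine is added for comfort, and hyaluronic acid is background treatment. A plan may leave contraindications to such products to the treating clinician. Being eligible does not compel an injection, and the undescribed history collection, or consent pages not available for review, may already cover allergy. The prevalence range has no source in the documents, so the probabilities only restate it. The fix also costs more than a line of text, because every protocol amendment needs committee approval.

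Much of this stands. Allergy may be asked about in practice, the probabilities should carry little weight, and the amendment process is a real cost. The textual point survives. The documents do not say that these contraindications are left to clinicians. The therapists who give the injections are described as taking no part in other trial processes, so as written they do not screen. Glucocorticoid allergy would be caught by usual practice just as readily, yet it was thought worth writing down; naming one injected product out of three is hard to justify on that ground.

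**Conclusion.** The concern holds as a minor point about an incomplete list; no two sections contradict each other. Followed exactly, the eligibility rule admits a person with a known allergy to a product that both arms are planned to receive. This rests on the text alone and needs no prevalence figure. If one is wanted, the expected number among 60 participants is below one across the assumed range, and lower still if staff ask. There is no material effect on the treatment comparison and none on alpha, power or sample size. It is worth correcting for safety, and it does not call the trial's results into question.

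**What to change.** Reword protocol exclusion 1 along these lines: *known allergy or hypersensitivity to the glucocorticoid preparation, lidocaine, hyaluronic acid, or any of their components*. Add an explicit allergy question to the history taken at screening. Change the copied list in SAP 5.1 to match, for consistency only.

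The drafting cost is one line and one question. The procedural cost is set out under Protocol amendments: approval by the governance and ethics committees, notice to the principal investigator at each of the four centres, filing of the revised protocol in the site files, and an entry in the trial registry. Combining the change with any other amendment would spread that cost. On recruitment, under the same 0.1% to 1% assumption, at most 0.6 of 60 otherwise eligible participants would be lost on average.

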### Randomization and blinding

Using block randomization in block size of four, eligible participants in each center will be assigned to the treatment or placebo group with a 1:1 allocation rate based on computer-generated random numbers. A staff member who is not involved in this trial will pack the drugs with a random number indicated on each of the packages. Allocation concealment will be ensured and Allocation results will be not revealed until the completion of final data analyses. Double-blind (participants & researchers

including outcome assessors and statisticians) design will be applied in this trial. Because of the different appearance of the injection drugs, the physical therapists for the injections are not blinded, and they will not be involved in other processes of this trial. During the period of preparing and injecting the drug, participants will be out of sight of the injection drugs. Unblinding will be conducted after all the data analyses are obtained. Emergency unblinding will be permissible when a serious adverse event happens, and patients who are unblinded will be withdrawn from the trial.

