## **Data management**

Research Electronic Data Capture (REDCap), a secure web-based application, will be applied to facilitate the data collection throughout the study. It has a function of self-monitoring in data entry which maximizes data quality. After each follow-up, the researcher will timely input the obtained data into REDCap, and a backup REDCap

data will be regularly stored at the principal study center. At the completion of the follow-up, the MR images will be assessed. After all the data are obtained, unblinding will be undertaken. In this trial, the two-step unblinding method will be applied. In the first step of unblinding, the participants will be classified into group A and group B for data analyses. After that, the second step of unblinding will assign the two groups to the treatment group or placebo group.

The participants are allowed to withdraw at any time throughout the study. If the participants withdraw from the study before the end of the trial, they are asked to have data collected including MRI assessment. The reason and date of the withdrawal will be recorded and the data before the withdrawal will be asked to retain.

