## Statistical plan

Baseline characteristics will be displayed in descriptive statistics according to the data type. Continuous variables with normal distribution will be displayed by means and standards deviation. Continuous variables with non-normal distribution will be displayed by median and interquartile range. Category variables will be displayed by proportion.

The intention-to-treat analysis will be the primary analyses method. The per-protocol analysis will be the second analyses method where the per-protocol population is defined as participants completed four follow-ups without major protocol deviations. There is no interim analysis in this research. Missing data due to dropout and nonresponses will be addressed using multiple imputations with chain equations. For each treatment group, imputations will be performed separately based on the baseline characteristics and the non-missing values at other time points of the missing variables with the assumption of data missing at random. Imputations will be performed separately for each treatment group and each outcome using baseline variables of age, sex, BMI, and study site and non-missing values of the outcomes at baseline and each follow-up with the assumption of data missing at random.

Mixed-effects regression models will be used to calculate treatment group differences with continuous measures. In the models, fixed effects will be follow-up time, baseline covariates (including age, sex, BMI, baseline value of the corresponding outcome), treatment, and interactions between follow-up time and baseline covariates and treatment. Study site and individual participant identification will be treated as the random intercepts and follow-up time as the random slop in the models. The overall treatment group differences will be calculated by the linear combination of the estimated coefficients. Wilcoxon rank-sum test will be used to analyze the difference in pain medication use between the treatment and placebo groups. Pain medication use will be classified as commenced/increased, unchanged, or discontinued/decreased. The chi-square test or Fisher's exact test will be used to compare the incidence of adverse reactions between the two treatment groups, and the number of adverse reactions will

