## **5.2. Withdraw/follow-up**

The participants are allowed to withdraw at any time throughout the study. If the participants withdraw from the study before the end of the trial, they are asked to have data collected including MRI assessment. The reason and date of the withdrawal will be recorded and the data before the withdrawal will be asked to retain.

In instances where participants experience a serious adverse event leading to their unblinding, such circumstances will be considered equivalent to withdrawal from the trial. Participants who cannot be reached or fail to return within a 16-week timeframe will be classified as lost to follow-up.

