### **6.2. Analysis methods**

Baseline characteristics will be displayed in descriptive statistics according to the data type. Continuous variables with normal distribution will be displayed by means and standards deviation. Continuous variables with non-normal distribution will be displayed by median and interquartile range. Category variables will be displayed by proportion.

The intention-to-treat analysis will be the primary analyses method. The per-protocol analysis will be the second analyses method where the per-protocol population is defined as participants completed four follow-ups without major protocol deviations. There is no interim analysis in this research. Mixed-effects regression models will be used to calculate treatment group differences with continuous measures. In the models, fixed effects will be follow-up time, baseline covariates (including age, sex, BMI, baseline value of the corresponding outcome), treatment, and interactions between follow-up time and baseline covariates and treatment. Study site and individual participant identification will be treated as the random intercepts and follow-up time as the random slop in the models. The overall treatment group differences will be calculated by the linear combination of the estimated coefficients. Wilcoxon rank-sum test will be used to analyse the difference in pain medication use between the treatment and placebo groups. Pain medication use will be classified as commenced/increased, unchanged, or discontinued/decreased. The chi-square test or Fisher's exact test will be used to compare the incidence of adverse reactions between the two treatment groups, and the number of adverse reactions will be reported as the number of participants reporting at least one adverse reaction.

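### Participants unblinded after a serious adverse event are withdrawn although all trial treatment is given at baseline, so later scheduled outcome and adverse-event data may go uncollected, and the gap is handled only under MAR

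*Combined protocol and SAP*

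**What the plan says.** The protocol section on randomization and blinding permits emergency unblinding after a serious adverse event and adds that "patients who are unblinded will be withdrawn from the trial". SAP 3.2 repeats the rule. SAP 5.2 adds that, where a serious adverse event leads to unblinding, "such circumstances will be considered equivalent to withdrawal from the trial".

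On treatment, the protocol's Intervention section says "Each group will receive two injections at baseline": the fat-pad injection of glucocorticoid or saline, and the background hyaluronic acid. No later trial treatment is described.

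On withdrawal, the protocol (Data management) and SAP 5.2 both say of participants who leave early that "they are asked to have data collected including MRI assessment" and that "the data before the withdrawal will be asked to retain". Neither gives the timing of that collection or says that the remaining scheduled assessments go ahead.

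On analysis, SAP 6.2 states: "The intention-to-treat analysis will be the primary analyses method". The protocol's Statistical plan says: "Missing data due to dropout and nonresponses will be addressed using multiple imputations with chain equations". Both documents assume MAR and impute separately by arm from age, sex, BMI, study site and the outcome's observed values at other times.

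**The concern.** Withdrawal after unblinding can serve a purpose when dosing is still to come. Here none remains, so the rule's practical effect is on data collection. The trigger occurs after randomisation and may depend on the arm. Any resulting missingness could be informative, and it would come from the plan's own rule rather than from the participant's choice.

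Three things are at stake:

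- **VAS pain (primary).** The remaining scores at weeks 4, 8 and 12 may not be obtained.
- **Effusion-synovitis volume (primary).** It has one scheduled post-baseline measurement, at week 12. An MRI taken early, at withdrawal, is not that measurement, and the plan does not say how it would enter the analysis.
- **Safety.** Adverse-event enquiries after unblinding may stop in participants who have just had a serious event. The protocol's abstract names safety as an aim, the introduction says that no earlier study has injected drugs at this site, and there is no Data Monitoring Committee.

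**Working it through.** **1. What the rule can change.** Setting the sections side by side:

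| Question | What the documents give |
|---|---|
| Does withdrawal stop later trial treatment? | No. Both injections are at baseline (Intervention). |
| Are earlier data kept? | Retention is sought (Data management; SAP 5.2). |
| Are data sought from those who withdraw? | Yes, including MRI; timing not stated. |
| Do scheduled visits and adverse-event enquiries continue? | Not stated. |
| Do these participants leave the ITT set? | No text says so; missing outcomes are imputed. |
| Does the imputation model include a serious-event or unblinding term? | No (Statistical plan; SAP 6.3). |
| Is there a sensitivity analysis for departures from MAR? | None stated. |
| Do they stay in the per-protocol set? | Probably not: it needs all four follow-ups (SAP 4.2 and 6.2). |

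If an early MRI cannot stand in for week 12, the volume is imputed from age, sex, BMI, site and the baseline volume alone.

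**2. The plan's own sample size.** Inputs from the protocol's Sample size section and SAP 3.3: δ = 19.9 mm, σ = 24.2 mm, Zα = 1.96, Zβ = 0.842, 20% loss.

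- n per group = 2 × [(1.96 + 0.842) × 24.2 / 19.9]² = 23.22, rounded up to 24.
- With 20% loss: 24 / 0.80 = 30 per group.

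Both figures reproduce.

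**3. Size of one case.** 1/30 = 3.3% of an arm. The documents give no serious-event or unblinding rate, so I assume k = 1 to 3 cases, all in one arm.

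**4. Power.** Power = Φ(19.9 / [24.2 × √(1/n₁ + 1/n₂)] − 1.96). I start from 24 evaluable per arm, that is, with the 20% allowance already used up:

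| Extra losses in one arm | n₁, n₂ | Power |
|---|---|---|
| 0 | 24, 24 | 81.3% |
| 1 | 23, 24 | 80.5% |
| 2 | 22, 24 | 79.6% |
| 3 | 21, 24 | 78.6% |

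This counts a lost participant as contributing nothing. Imputation from earlier VAS scores could recover part of that.

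**5. Bias.** If k of 30 in one arm are imputed and their true VAS change differs from the imputed value by D mm on average, the arm mean is off by k × D / 30. D is an assumption; I show 10 to 40 mm.

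| k | D = 10 | D = 20 | D = 30 | D = 40 |
|---|---|---|---|---|
| 1 | 0.3 mm | 0.7 mm | 1.0 mm | 1.3 mm |
| 2 | 0.7 mm | 1.3 mm | 2.0 mm | 2.7 mm |
| 3 | 1.0 mm | 2.0 mm | 3.0 mm | 4.0 mm |

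The group difference moves by the same amount if the other arm is unaffected. The target difference is 19.9 mm.

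**The case against.** The strongest reply is that the plan already softens the rule and that the numbers are small. Much of this stands, and it rules out several stronger readings that a reader might infer:

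- **That data are discarded.** They are not. Data are asked for when a participant leaves, including MRI, and earlier data are to be kept. Because SAP 5.2 equates unblinding with withdrawal, these provisions cover unblinded participants. The triggering event itself precedes withdrawal.
- **That ITT is breached by exclusion.** No text removes these participants. They remain in their randomised arm through imputation. The issue is avoidable missing values under an ITT analysis.
- **That adverse-reaction incidence is necessarily undercounted.** The endpoint counts participants with at least one reaction. If the triggering event is judged a reaction, the participant is already counted. A case is lost only if that event was judged not to be a reaction, none was recorded before it, and a first one appears after withdrawal.
- **That the loss is treatment-related.** This is possible, but the documents do not show it.
- **That values are borrowed from participants without serious events.** Imputation is by arm and uses the participant's own other values. Unblinding is only permitted, not required, after a serious event, so some participants with such events may stay in follow-up and inform the model.

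It can also be said that the design allows for 20% loss, and that someone with a serious event may be unable to attend whatever the rule. Both points are fair.

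A last argument is that unblinded self-reports are unreliable. That applies to VAS, WOMAC, AQoL-4D and reported medication use. It does not apply to the MRI reading, which is done after follow-up by blinded assessors.

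What the reply does not answer is that neither document says the remaining assessments continue, and that no analysis tests MAR for values lost after a serious event.

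**Conclusion.** The point holds in a limited form. The rule protects no later dosing and can only shorten follow-up. The week-12 VAS, the only post-baseline MRI and later adverse-event enquiries may be missed in participants selected by a serious adverse event, and the plan handles the gap under MAR alone.

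The expected effect is small. One case with an imputation error of 10 to 40 mm moves the arm mean by 0.3 to 1.3 mm. Three cases in one arm at 40 mm give 4.0 mm and, if the loss allowance is already spent, power of 78.6%. These figures rest on assumed values of k and D. They would grow only if several serious events led to unblinding, mostly in one arm. The change is worth making because it is cheap and removes a loss that the plan would otherwise impose on itself, not because the primary result is likely to turn on it.

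**What to change.** Replace the withdrawal rule in the protocol (Randomization and blinding), SAP 3.2 and SAP 5.2 with:

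*Unblinded participants remain in follow-up for all scheduled outcome and adverse-event assessments to week 12 unless they withdraw consent, and are analysed as randomised. The date and reason for unblinding are recorded. MRI continues to be read by blinded assessors.*

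Add two sensitivity analyses to SAP 6.2 and 6.3:

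- (a) Exclude all self-reported outcomes collected after unblinding: VAS, WOMAC, AQoL-4D and pain medication use. Restricting this to VAS would leave the other self-reports untested.
- (b) Vary the MAR assumption for values that are still missing, for example by delta-adjusted imputation over a stated range. Include the values set aside under (a), since otherwise (a) brings back the same reliance on MAR.

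The cost is an amendment to the wording of both documents and a short addition to the analysis code. No new visits are needed. The downside is that a few self-reported scores, and a few judgements on whether an event is an adverse reaction, will be made after unblinding. These should be flagged in the data and in the report.
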